|  | 
 
- Cycle 1: Days 8, 9, 15, and 16: 36 mg/m^2
 
 
*Alternatively, intermediate dose escalation (to 27mg/m^2 on Days 8, 9 of Cycle 1) will be allowed at the treating physician's discretion.
 
 
- Cycle 2-8 36 mg/m^2 (or last best tolerated dose) of carfilzomib on Days 1, 2, 8, 9 and 15, 16
 
- Cycle 9-24: 36 mg/m^2 (or last best tolerated dose) of carfilzomib on Days 1, 2 and 15, 16
 
 
Lenalidomide
 
 
- Cycle 1-24 PO at 25 mg per dose (or at last best tolerated dose) on Days 1- 21
 
 
Dexamethasone
 
Dexamethasone will be administered between 30 minutes and 4 hours preceding carfilzomib (on days that they coincide), as follows:
 
 
• Cycles 1-4: 40 mg PO (subjects < 75 years) or 20 mg PO (subjects ≥ 75 years) per week
 
• Cycles 5-24: 20 mg PO per week
 
 
For weeks of daratumumab injection, dexamethasone dose is split into two doses: half the dose prior to daratumumab infusion and half the dose the day after.
 
Split weekly dosing on other days (e.g. 10 mg on Day 1 and 10 mg on Day 2, etc.) is permitted with approval from Lead Principal Investigator.
 
Dexamethasone given on days without carfilzomib (on Days 22 and 23 of Cycles 1-8) may be self-administered by the subject on an outpatient basis. If Day 2 of carfilzomib dosing is delayed (i.e., Day 2, 9, 16) 4 mg of dexamethasone premedication is required to be used prior to second treatment. Missed doses will not be replaced during a cycle. Missed doses of dexamethasone will not be made up.
 
Treatment Overview
 
Cycles 1 through 4 are considered D-KRd induction cycles, Cycle 5-8 are D-KRd consolidation, and cycles 9-24 D-KRd are maintenance cycles.
 
After Cycle 4, subjects who are deemed candidates for ASCT will proceed to stem cell harvest as per institutional guidelines. However, these subjects will not proceed straight to ASCT and will have cells frozen down for a potential future transplant at progression or unacceptable toxicity after
 |

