### **4 INVESTIGATIONAL PLAN**

#### **4.1 Overview of Study Design and Dosing Regimen**

This study will be a multi-center, open-label, phase 2 study, enrolling subjects with newly diagnosed MM requiring systemic chemotherapy. All dosing schedule is based on 28-day cycles. Subjects will receive treatment until disease progression or unacceptable toxicity (whichever occurs first).

Enrolled subjects will initially receive lenalidomide at 25 mg per dose (see below if previously unable to tolerate 25 mg) on Days 1-21. Carfilzomib will be dosed at 20 mg/m^2 on Days 1 and 2 and 36mg/m^2 thereafter (Days 8,9,15, and16). Alternative escalation will be allowed on Cycle 1 if the treating

investigator considers it necessary as follows: 20 mg/m^2 on Days 1 and 2 escalated to 27 mg/m^2 on Days 8 and 9, and then to 36 mg/m^2 on Days 15 and 16. Daratumumab will be administered by subcutaneous injection, provided as a fixed-dosed of 1800 mg and 30,000 units hyaluronidase per 15 mL (120 mg and 2,000 units/mL) for all cycles. The injection will be given by manual push over 3 to 5 minutes in the abdominal SC tissues in left/right locations, alternating between individual doses. Dexamethasone will be dosed at 40 mg PO per week for subjects < 75 years and 20 mg PO per week for subjects ≥ 75 years during Cycles 1-4. Dose modifications will be mandated based on aggressive schedule of dose modification for toxicities as per specific guidelines. Otherwise, patients will continue at their best tolerated dose of lenalidomide on Days 1-21 and their best tolerated dose of carfilzomib on Days 1, 2, 8, 9, 15, 16 in Cycles 1-4 and Days 1, 2, 15, 16 in Cycles 5-8.

All subjects will have monthly clinic visits for disease assessments. Treatment will continue on protocol for up to 24 months or if carfilzomib, lenalidomide and daratumumab are permanently discontinued. If dexamethasone is discontinued due to toxicity, carfilzomib, lenalidomide and daratumumab may be continued if tolerated without dexamethasone. Toxicity will be graded using the National Cancer Institute Common Terminology Criteria for Adverse Events version 4. Patients who complete 24 cycles will then continue single-agent lenalidomide at best tolerated dose (up to 25 mg) in 28-day cycles. This regimen will continue until there is progression of the disease or the toxicities require discontinuation of the drug.

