#### **Recommended Concomitant Therapy for Daratumumab SC Dosing:**

All participants will receive the following medications 1 to 3 hours prior to each study drug administration:

- An antipyretic: Acetaminophen 650 mg PO
- An antihistamine: diphenhydramine 25-50 mg IV or PO or equivalent. Avoid IV use of promethazine. After Cycle 6, if a participant has not developed an infusion-related reaction and is intolerant to antihistamines, modifications are acceptable as per investigator discretion.

- Corticosteroids as indicated in 6.3.3.
- Montelukast 10 mg PO
- For patients considered high-risk for an infusion reaction because of underlying pulmonary conditions, inhaled or nebulized albuterol along with inhaled combined long-acting beta agonist + corticosteroid can be considered at the discretion of the investigator.

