### 6.3.3 Dexamethasone Administration

Dexamethasone will be administered between 30 minutes and 4 hours preceding carfilzomib (on days that they coincide), as follows:

Dexamethasone will be administered between 30 minutes and 4 hours preceding carfilzomib and between 1 to 3 hours preceding daratumumab (on days that they coincide), as follows:

- Cycles 1-4: 40 mg PO (subjects < 75 years) or 20 mg PO (subjects ≥ 75 years) per week
- Cycles 5-24: 20 mg PO per week

For weeks of daratumumab injection, dexamethasone dose is split into two doses: half the dose prior to daratumumab infusion and half the dose the day after.

- Split weekly dosing for all other days (e.g. 10 mg on Day 1 and 10 mg on Day 2, etc.) is permitted with approval from Lead Principal Investigator.
- Dexamethasone given on days without carfilzomib (on Days 22 and 23 of Cycles 1-8) may be self-administered by the subject on an outpatient basis.
- If Day 2 of carfilzomib dosing is delayed (i.e., Day 2, 9, 16) 4 mg of dexamethasone premedication is required to be used prior to second treatment. Missed doses will not be replaced during a cycle. Missed doses of dexamethasone will not be made up.

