21. Peripheral blood and bone marrow aspirate samples collected at screening, end of cycle 8, time of response (to confirm complete response), end-of-treatment visit, and yearly after end of treatment for up to 2 years. Buccal mucosa swab will be collected at screening only.
22. AEs will be collected from the time of signing informed consent. 30 days following the last dose of D-KRD, patients will be considered to be off-study so no toxicities will be recorded following this period. All concomitant medications must be recorded on the concomitant medications case report form from 21 days before Day 1 through 30 days following the last dose of study drugs.
23. Assessment for disease progression in subjects who did not progress during treatment. At least every 3 months (+/- 30 days) for 5 years from safety follow-up visit (which must be 28days (+/- 3 days) post-last study treatment).
24. Lenalidomide must be prescribed through and in compliance with the Revlimid REMS® program of Celgene Corporation. Prescriptions must be filled within 7 days. Consideration should be given to prescribing lenalidomide 5 to 7 days in advance of Day 1 of each cycle to allow time for required patient and prescriber surveys, and drug shipment to patient. Any unused Revlimid® (lenalidomide) should be returned to the patient for disposition in accordance with the Revlimid REMS® program.
25. Cycles 1-8: Days 1, 2, 8, 9, 15 & 16. Cycles 9-24 Days 1, 2, 15 and 16.
26. Daily on Days 1-21 followed by a 7-day rest period every 28 days. On day coinciding with carfilzomib administration, lenalidomide should be taken at least 4 hours after the carfilzomib dose and may be self-administered at home by the subject. On days that carfilzomib is not administered, lenalidomide should be taken at approximately the same time each day.

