27. Days 1, 8, 15 and 22. Dexamethasone is given between 30 minutes and 4 hours before carfilzomib on days they coincide. Dexamethasone will be dosed at 40 mg PO per week during Cycles 1-4 and 20 mg PO per week during Cycles 5-24. Cycles 9-24 represent the D-KRD Maintenance Phase of therapy and the dose of dexamethasone will remain 20 mg on days 1, 8, 15 and 22. For weeks of daratumumab injection, dexamethasone dose is split into two doses: half the dose prior to daratumumab infusion and half the dose the day after. Split weekly dosing for all other days (e.g. 10 mg on Day 1 and 10 mg on Day 2, etc.) is permitted with approval from Lead Principal Investigator. Dexamethasone given on days without carfilzomib (on Days 22 and 23 of Cycles 1-8) may be self-administered by the subject on an outpatient basis. If Day 2 of carfilzomib dosing is delayed (i.e., Day 2, 9, 16) 4 mg of dexamethasone premedication is required to be used prior to second treatment. Missed doses will not be replaced during a cycle. Missed doses of dexamethasone will not be made up. Single-agent lenalidomide maintenance therapy, is recommended using last tolerated dose of lenalidomide for 21 days in 28 day cycles after D-KRD protocol treatment (Cycles 1-24) is completed.
28. Patients will be followed for survival and development of any new cancers, at least every 3 months. Reports of any death should include date of death and specific cause (disease under study or specify other cause).
29. Evaluations at the end of Cycle 8 may be done on Day 1 of the next Cycle 9.

30. Plasmacytoma evaluation is required at screening only and may be completed as physical exam or imaging if indicated and at the treating investigator's discretion. After screening, plasmacytoma evaluation is required only for patients who have no other measurable disease and/or at investigator's discretion.

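### Appendix 8, footnote 27 gives dexamethasone 40 mg per week in Cycles 1-4 with no age condition; the synopsis and Sections 4.1 and 6.3.3 set 20 mg from age 75

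*Protocol*

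**What the plan says.** The protocol states the dexamethasone dose for Cycles 1-4 in four places.

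- **Synopsis, Study Design:** 40 mg per week below age 75, otherwise "20 mg PO (subjects ≥ 75 years) per week".
- **Section 4.1:** 40 mg per week below age 75, and "20 mg PO per week for subjects ≥ 75 years during Cycles 1-4".
- **Section 6.3.3, the section on dexamethasone administration:** "Cycles 1-4: 40 mg PO (subjects < 75 years) or 20 mg PO (subjects ≥ 75 years) per week".
- **Appendix 8, footnote 27:** "Dexamethasone will be dosed at 40 mg PO per week during Cycles 1-4 and 20 mg PO per week during Cycles 5-24".

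The dexamethasone row of the Cycles 1-4 grid in Appendix 8 is marked with footnote 27. The footnote also carries over several rules from Section 6.3.3: splitting the dose, self-administration on days without carfilzomib, the 4 mg premedication when the second carfilzomib day is delayed, and the missed-dose rule ("Missed doses of dexamethasone will not be made up"). It does not carry over the age split and does not refer the reader to Section 6.3.3.

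**The concern.** The first three places make the Cycles 1-4 dose depend on age, and the fourth does not. For a patient aged 75 or over the four statements cannot all be followed.

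The footnote is an operative instruction. It states milligrams and is attached to the dosing row of the schedule. A site that treats from the schedule could give an older patient twice the intended weekly steroid dose.

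The conflict also reaches two other rules in the protocol. The Overdose section under 8.3.4 counts any oral amount above the protocol-specified dose as an overdose, to be reported in the case report form. With two specified doses, it is unclear whether 40 mg at age 75 counts. Table 6-4 has separate reduction ladders for the 40 mg and 20 mg starting doses, so the starting dose also decides which ladder applies.

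**Working it through.** This is a comparison of texts with simple dose arithmetic. The protocol offers no figure of its own to reproduce, and no sample size, power or alpha value depends on the point.

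**1. Are patients aged 75 or over eligible?** Section 5.1 sets a minimum age of 18 and no maximum, and admits transplant and non-transplant candidates alike. Section 5.2 excludes frail non-transplant candidates but sets no age limit. Three sections specify a dose for age 75 or over, so the protocol expects such patients.

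**2. The statements side by side.**

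| Source | Cycles 1-4, under 75 | Cycles 1-4, 75 or over | Cycles 5-24 |
|---|---|---|---|
| Synopsis | 40 mg/week | 20 mg/week | 20 mg/week |
| Section 4.1 | 40 mg/week | 20 mg/week | not stated there |
| Section 6.3.3 | 40 mg/week | 20 mg/week | 20 mg/week |
| Appendix 8, footnote 27 | 40 mg/week | 40 mg/week (no age condition) | 20 mg/week |

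The footnote does not say that it applies to everyone. It does so only because it has no qualifier. The conflict is confined to one cell: age 75 or over, Cycles 1-4.

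**3. Size of the discrepancy for one patient in that cell.** Footnote 27 lists Days 1, 8, 15 and 22, so there are four weekly doses per 28-day cycle. If all are given:

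- Per week: 40 mg against 20 mg; ratio 40 / 20 = 2; difference 20 mg.
- Per cycle: 40 × 4 = 160 mg against 20 × 4 = 80 mg; difference 80 mg.
- Over Cycles 1-4: 160 × 4 = 640 mg against 80 × 4 = 320 mg; difference 320 mg.

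**4. Effect on the reduction ladder.** In Table 6-4 the 40 mg ladder runs 32, 24, 20 mg. A patient of 75 or over wrongly started at 40 mg would reach the intended starting dose of 20 mg only at the third reduction. From 20 mg the ladder runs 12, 8, 4 mg.

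**5. Where a site is sent for dosing.** Footnote 25 gives only carfilzomib days ("Cycles 1-8: Days 1, 2, 8, 9, 15 & 16. Cycles 9-24 Days 1, 2, 15 and 16"). Footnote 26 gives lenalidomide days ("Daily on Days 1-21 followed by a 7-day rest period every 28 days") with timing and self-administration advice, but no dose. For those two drugs the reader must go to Section 6.3. Footnote 27 states the dose, so the reader has less reason to look further. The Study Treatment row of Section 6.1.2 sends sites to Appendix 8 and to Section 7. Section 7 covers samples for MRD and correlative work and contains no dosing. Of the two places named in that row, only Appendix 8 gives a dexamethasone dose, and it is the one without the age split.

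**The case against.** The case on the other side is about weight, and much of it stands.

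- **The intended dose is not in doubt.** Three sections agree, among them the one devoted to dexamethasone administration. Section 6 introduces the study calendar as an overview, and the daratumumab premedication list in Section 6.2.2 sends steroid dosing to the right place ("Corticosteroids as indicated in 6.3.3"). A site must open Section 6.3 anyway for the carfilzomib and lenalidomide doses. All of this stands and lowers the chance of a dosing error.
- **The footnote is an abridgement.** It also leaves out the interval of 1 to 3 hours between dexamethasone and daratumumab that Section 6.3.3 gives, and it has no dose-reduction rules. Nor is it the only footnote with a dose in milligrams, since the daratumumab footnote has one too. This stands: footnote 27 should not be called a complete or unique instruction. But a summary that states a dose must state it correctly for every patient it covers.
- **Few patients, possibly none, are exposed.** Section 6.3.4 ends intravenous daratumumab under the current version, and Section 6.3.5 says that all patients are switching from it, with no new starts. On that reading only a patient aged 75 or over already in Cycles 1-4 could be affected. This is a fair limit, although not a settled one: Section 6.3.5 also describes observation on Cycle 1 Day 1, and Section 6.3.5.1 keeps a schedule for Cycles 1-2.
- **The Section 7 pointer is a separate slip.** That is so. Correcting it would not correct footnote 27. It belongs here only because that row is one route by which a site reaches the footnote.

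None of these points removes the contradiction.

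**Conclusion.** The concern holds. Footnote 27 is wrong as written for patients aged 75 or over in Cycles 1-4, where it gives twice the weekly dose set in the three other places. There is no discrepancy for younger patients or for Cycles 5-24.

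The milligram totals are per-patient figures. They assume that a site follows the footnote over the other sections and that every weekly dose is given. The protocol does not show how many patients this could reach under the current version, and the number may be zero. Nothing changes in the sample size, the primary test, the endpoints or the analysis. The reason to act is patient safety at almost no cost, so it should be fixed at the next amendment.

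**What to change.** Add the age condition to footnote 27, matching Section 6.3.3: for Cycles 1-4, 40 mg per week under 75 years and 20 mg per week at 75 years or over; for Cycles 5-24, 20 mg per week as now. A reference to Section 6.3.3 in the footnote would help to keep the two aligned.

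In the Study Treatment row of Section 6.1.2, replace the pointer to Section 7 with one to Section 6.3.

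The cost is one parenthesis and one cross-reference. Data collection and analysis do not change.
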